## Abstract

**Background:**

The aim of the SPHERE study is to design, implement and evaluate tailored practice and personal care plans to improve the process of care and objective clinical outcomes for patients with established coronary heart disease (CHD) in general practice across two different health systems on the island of Ireland.

CHD is a common cause of death and a significant cause of morbidity in Ireland. Secondary prevention has been recommended as a key strategy for reducing levels of CHD mortality and general practice has been highlighted as an ideal setting for secondary prevention initiatives. Current indications suggest that there is considerable room for improvement in the provision of secondary prevention for patients with established heart disease on the island of Ireland. The review literature recommends structured programmes with continued support and follow-up of patients; the provision of training, tailored to practice needs of access to evidence of effectiveness of secondary prevention; structured recall programmes that also take account of individual practice needs; and patient-centred consultations accompanied by attention to disease management guidelines.

**Methods:**

SPHERE is a cluster randomised controlled trial, with practice-level randomisation to intervention and control groups, recruiting 960 patients from 48 practices in three study centres (Belfast, Dublin and Galway). Primary outcomes are blood pressure, total cholesterol, physical and mental health status (SF-12) and hospital re-admissions.

The intervention takes place over two years and data is collected at baseline, one-year and two-year follow-up. Data is obtained from medical charts, consultations with practitioners, and patient postal questionnaires.

The SPHERE intervention involves the implementation of a structured systematic programme of care for patients with CHD attending general practice. It is a multi-faceted intervention that has been developed to respond to barriers and solutions to optimal secondary prevention identified in preliminary qualitative research with practitioners and patients. General practitioners and practice nurses attend training sessions in facilitating behaviour change and medication prescribing guidelines for secondary prevention of CHD. Patients are invited to attend regular four-monthly consultations over two years, during which targets and goals for secondary prevention are set and reviewed. The analysis will be strengthened by economic, policy and qualitative components.

## Background

Coronary heart disease (CHD) is a common cause of death and an important cause of morbidity in Ireland. Secondary prevention of heart disease involves long-term management of risk factors among people who have been diagnosed with established CHD. The Scottish Intercollegiate Guidelines Network has defined secondary prevention as the 'identification and modification of risk factors by the introduction of lifestyle measures and pharmacological therapy and cardiac rehabilitation' [1]. Secondary prevention has been recommended as a key strategy for reducing levels of CHD [2,3]. Secondary prevention can be achieved by stopping smoking, making healthier food choices (including reducing fat intake and increasing intake of fruit, vegetables and fibre), becoming physically active, achieving an ideal weight, consuming alcohol in moderation, appropriate prescription of, and adherence to, pharmacological therapy, achieving blood pressure level at or under 140/90 mmHg and achieving a total cholesterol level at or below 5 mmol/l [3].

Most people with CHD regularly attend their general practitioner and general practice has been highlighted as an ideal setting for secondary prevention initiatives [2]. Previous studies of provision of secondary prevention in general practice have identified sub-optimal levels [4-6]. Current indications suggest that there is considerable room for improvement in the provision of secondary prevention for patients with established heart disease on the island of Ireland [7]. Recent data from the national Heartwatch programme suggest that 44% of Irish patients with established heart disease have a systolic blood pressure above the recommended guidelines of 140 mmHg, and that 36% have a baseline cholesterol level of greater than 5 mmol/l ([name], personal communication). In a survey of secondary preventive care of 1,600 patients, from 35 randomly selected general practices in the west of Ireland, results were as follows: 23% of patients were regular smokers, 45% had cholesterol readings greater than 5 mmol/l and 34% had blood pressure readings greater than 140/90 mmHg. In addition, GP records were found to be incomplete, with 38% of patients with no record of smoking status and 25% with no cholesterol reading. Information from Northern Ireland suggests a similar situation: a recent survey found that among patients with a confirmed diagnosis of CHD 18% smoked, 25% had a body mass index (BMI) greater than 30, 51% had a systolic blood pressure greater than 140 mmHg and approximately 50% had cholesterol levels greater than 5 mmol/l [8].

Randomised controlled trials have investigated the effectiveness of secondary prevention interventions including health visitor advice [9], nurse-led secondary prevention clinics [10,11], outreach visits to practices by nurses trained in cardiovascular risk factor recording [12], provision of specialist liaison nurses to bridge the gap between secondary and primary care [13], postal prompts to patients to encourage lifestyle changes [14], audit and systematic recall of patients from disease registers [15], combined training to all practice staff in information systems and evidence-based medicine [16] and a cognitive-behavioural disease management programme [17].

These trials have reported a number of successful outcomes, including increased physical activity [9,10,17], improved diet [9,10,17], increased health functioning [9,10,17], increased patient assessment and recording of risk factors [12,14-16], increased rate of consultation for coronary heart disease [14], improvements in medication prescribing [10,15], improved lipid management [10,14,16], reduction in cholesterol level [16], improved blood pressure management [10], increased lifestyle advice provision [14] and reduced anxiety and depression [17].

However, with the exception of the PIER trial [16] which achieved significant reductions in cholesterol levels among intervention group patients, trials have not achieved significant improvements in objective biophysical risk factors, such as blood pressure or cholesterol levels.

A systematic review identified twelve randomised trials of disease management programmes for patients with established heart disease [18]. It concluded that such programmes *do *improve processes of care, reduce hospital admissions and enhance quality of life and functional status in patients with CHD. However, the reviewers noted that studies included imprecise descriptions of both the interventions and the usual care provided to the control groups, resulting in an inability to determine the incremental benefits of the various components of each intervention. Reviewers concluded that several important issues require further clarification, including the optimal mix of interventions and the cost-effectiveness or the economic impact of such interventions. Another earlier systematic review [19] also noted both the lack of detail provided of complex health service interventions, especially in the description of the usual care provided to control groups, and the need for the careful design and evaluation of different implementation models of secondary prevention.

Further possible explanations for the lower than expected clinical impact of secondary prevention interventions to date include inadequate consideration of doctors' and patients' perspectives on heart disease, lack of patient-centredness of the intervention and a failure to tailor practice interventions to individual patients and practices [13]. Wiles [20], utilising a qualitative approach as part of the SHIP study, especially emphasised the failure of 'official accounts' to acknowledge patient perceptions as a key feature in people's reluctance to adopt lifestyle change.

There is substantial evidence that structured systematic care is important to improve levels of secondary prevention of coronary heart disease, and an effective register, recall system and routine audit of care are essential components of such a system [13,21]. There is also some evidence to suggest that nurse-led clinics [10], cognitive behavioural interventions [17,22,23] and tailored training identified by practice staff [16] are effective in improving secondary prevention in general practice and facilitating patients to make lifestyle changes.

A recent Cochrane review [24] of interventions to implement prevention in primary care highlighted the need to tailor interventions to address specific barriers to change in a particular setting. The review also concluded that multi-faceted interventions may be more effective than single interventions, as more barriers to change can be addressed. The authors of the review recommend that future research should analyse barriers to change and report interventions to implement preventive services in more detail, to clarify how interventions relate to specific barriers. Since such complex interventions are likely to be more costly than single interventions, these reviewers also advise that economic evaluations should be included in future studies.

The SPHERE Study aims to take these recommendations on board in developing an intervention to improve secondary prevention of CHD in general practice in Ireland. The SPHERE study involves the implementation of a structured systematic programme of care for patients with CHD attending general practice. The SPHERE intervention is multi-faceted and has been developed to respond to the barriers and solutions to optimal secondary prevention identified in preliminary qualitative research with practitioners and patients. The delivery of the intervention is tailored as much as possible to the needs of practices and patients. The process of the intervention will be documented and described in sufficient detail to allow replication of the intervention and to enable identification of effective intervention components. The intervention will be implemented over a 24 month period, with data collection at baseline, 12 months and 24 months. Data collection at these time points will enable identification of any initial and/or sustained changes effected by the intervention. An economic evaluation of the intervention will be carried out. The implementation of the intervention will be monitored throughout the duration of the trial and documented.

In summary, SPHERE will add to what is already known in respect of secondary prevention in primary care, i.e.

• that structured programmes, with continued support and follow-up of patients, help improve recording of process measures of preventive care, patients' functional status, quality of life and lifestyle change [9-11,15,17,25].

• prompts to patients improve their attendance but there is no associated change in measures of risk [13,15].

• structured recall programmes which do not take account of individual practice needs improve recording but not prescribing [15]; provision of training, tailored to practice needs of access to evidence of effectiveness of secondary prevention is associated with improved prescribing [16]

• patient centred consultations impact positively on health outcomes [26] but must be accompanied by attention to disease management guidelines to achieve clinical objectives [27].

SPHERE will:

• record organisational detail of care, in both intervention and control practices

• provide information and training tailored to practices' needs for delivery of secondary prevention

• support patient centred consultations and practitioners' adherence to disease management guidelines.

## Aim

To design, implement and test tailored practice and personal care plans to improve the process of care and objective clinical outcomes for patients with established coronary heart disease in general practice in Ireland.

## Design

Cluster randomised controlled trial, with practice-level randomisation to intervention and control groups.

## Random Selection of Practices and Patients

### Practice identification (48 practices, 16 at each centre)

The same method is followed by each centre in Belfast, Dublin and Galway for their respective regions of the Eastern Health and Social Services Board, the South Western Area Health Board and the Western and North Western Health Boards.

Lists of all practices meeting eligibility criteria are generated by the research nurses in each centre (see 'practice eligibility' section below for criteria). Practices are then allocated a number and randomly selected from the lists in each region by an individual independent of the research team using computer-generated random numbers. The practice manager or lead general practitioner in each practice is contacted by telephone by the research nurse to determine their interest in receiving information about the trial. With their agreement, information is posted to the practice (see additional file 1: Appendix A) and arrangements are made for a member of the research team to visit the practice to discuss their participation in the study.

During this meeting the research nurse explains the study to practice staff and gets commitment to the study, indicated by a signature, from practice staff (at least one GP, one practice nurse and one administrator). A Practice Implementation Plan is completed (see additional file 1: Appendix A) and all practice staff are invited to review and approve it. Practices that agree to participate are offered an honorarium of €1000 or the Sterling equivalent upon completion of the study.

If selected practices decline to participate or confirm that they do not meet the eligibility criteria, the next practice on the list is selected. Relevant details (number of whole-time equivalent (WTE) practitioners, list size and reason for not being recruited or not agreeing to participate) are recorded for those practices which are not recruited.

### Patient identification (20 patients in each practice)

Participating practices compile a list of all eligible patients (see 'patient eligibility' section below for detail) from their practice and allocate a number to each patient from 1 to Y (where Y is the total number of patients on the list). Research nurses assist the practices in using a list of random numbers to select patients for participation (see additional file 1: Appendix A). A confidentiality agreement will be signed between research nurses and practice staff, to ensure that normal ethical procedures governing each practice are adhered to. Selected patients are posted an invitation letter, information sheet and reply slip (see additional file 2: Appendix B) as well as a questionnaire (see additional file 3: Appendix C). Patients who do not respond within ten days are contacted by a member of the practice staff to ascertain interest in participation. If selected patients do not confirm that they fulfil the eligibility criteria or decline to participate, the next patient on the list is selected until the quota of 20 is reached. The age, gender and diagnostic inclusion criteria for those who do not participate are recorded. Patients who agree to participate are invited to attend the practice for a baseline data collection consultation.

Once sixteen practices have been recruited and the relevant patient baseline data collected, at each centre an individual independent of the research team using computer-generated random numbers will allocate, with prior stratification, practices to intervention or control groups. Stratification will be according to the WTE for practitioners (less-than-two and two-or-more). Patient identification and baseline data collection occur prior to practice randomisation to minimize potential bias introduced by researchers and practitioners being aware of their allocation to either the intervention or control group. For intervention practices, meetings will be arranged to develop tailored practice care plans, deliver appropriate training, and support practitioners in reviewing patients four monthly for two years. Control practices will be visited again after one year and after two years, at which time points follow-up data will be collected.

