**Figure 1 F1:**
[figure not shown]
Flow of Practices and Patients Throughout Trial.

Sample size calculations are based on the following:

• Power of 80% and alpha of 5%.

• Only patients agreeing to participate in the study and completing baseline data collection will be entered into the study. There will, therefore, be 100% uptake at the start of the study. Reasons for non-participation will be documented and recorded, and participation rates will provide a measure of the acceptability of this type of intervention to patients.

• A final completion rate of 70% is anticipated based on similar studies in the West of Ireland 7 (completion rate = 68.7%) and Dublin [28] (completion rate = 93%).

• Practice attrition of 12.5% has been allowed for (though practice attrition in another similar study was only 4% [28]).

• Improvements in the control group as a result of participation in a research study have been anticipated [25].

• Design effects are calculated using intracluster correlation coefficients from data from similar populations in Galway and Scotland ([name], personal communication).

A total sample size of 907 patients recruited from 46 practices gives a varying but minimum power of 80% to detect significant changes in proportions with poor blood pressure and cholesterol control, physical and mental well being (SF-12) and hospital readmissions at two years. (Detailed power calculations are given below). This allows for a final patient follow-up and retention rate of 70% and a practice attrition rate of 10%. The number of practices is rounded up from 46 to 48, to allow equal numbers of practices to be recruited in each of the three study centres. Sixteen practices will therefore be recruited in each of the three centres, eight intervention practices and eight control practices. Twenty patients are recruited in each practice. Final data analysis will incorporate modelling techniques that are more statistically efficient and will ensure greater power to detect significant changes in study outcomes.

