## Power Calculations – Further Detail

### Blood pressure

44% of Irish patients with established heart disease have a systolic blood pressure above recommended guidelines (SBP >140 mmHg) ([name], personal communication). Previous research indicates that an improvement of 20% can be anticipated in the control group [10]. Taking this into consideration, a sample size of 408 gives 80% power to detect a 50% reduction in the proportion of patients with a SBP above 140 mmHg (i.e. giving a proportion of 22%) in the intervention group with a corresponding 20% improvement in the control group. Other studies have indicated that it is possible to achieve similar targets in general practice populations with established coronary heart disease [15]. To take account of cluster randomisation, based on recruiting 15 patients per cluster, a design effect size of 1.15 and an intracluster correlation coefficient of 0.011 [4,10] suggests a sample size of 470 patients from 31 practices. Allowing for a final response rate of 70% and a practice attrition rate of 10% requires recruitment of 670 patients from 34 practices.

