### Randomised controlled trial analysis

Primary outcomes include:

• Blood pressure

• Total cholesterol

• Physical and mental status as measured by the SF-12

• Hospital re-admissions.

Secondary outcomes include:

• Measure of the process of care

SPHERE visits

Total number of GP visits

Total number of hospital OPD visits

Recording of risk factors in GP records

• Body Mass Index/Waist-Hip Ratio

• Exercise: Godin Leisure-Time Exercise Questionnaire

• Smoking status

• Diet: DINE, including question regarding portions of fresh fruit and vegetables

• Adherence to medication (Medication Adherence Report Scale MARS-5).

All results are analysed using SPSS and Stata statistical software. Statistical modelling is carried out using Stata statistical software which has a facility for complex survey sample analysis that allows for adjustments in data analysis based on design effects, planned or unplanned. Statistical significance will be taken at the 5% level for both primary and secondary outcomes. The analysis examines intervention vs control groups on study completion, as opposed to looking at changes in the intervention and control groups from baseline.

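### Allocation is done in one batch per centre after baseline data are in hand, yet no baseline outcome is used to balance it: an avoidable, modest loss of precision and credibility

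*Protocol article*

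**What the plan says.** All places are in the protocol article.

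- **Timing** (Patient identification): allocation happens "Once sixteen practices have been recruited and the relevant patient baseline data collected, at each centre an individual independent of the research team" draws it with computer-generated random numbers. The stated reason for waiting is to limit bias from researchers and practitioners knowing the allocation.
- **Stratification** (same section): "Stratification will be according to the WTE for practitioners (less-than-two and two-or-more". No other factor is named within a centre.
- **Split** (Sample Size Calculation): "Sixteen practices will therefore be recruited in each of the three centres, eight intervention practices and eight control practices". Centre is therefore balanced as well as practice size.
- **Size** (abstract and Sample Size Calculation): "recruiting 960 patients from 48 practices in three study centres (Belfast, Dublin and Galway" and "Twenty patients are recruited in each practice".
- **Analysis** (Randomised controlled trial analysis): "The analysis examines intervention vs control groups on study completion", in contrast to changes from baseline. Baseline as a covariate is neither planned nor ruled out there.

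**The concern.** Balancing on baseline outcomes is often impractical because clusters enter one by one and the data do not yet exist. Here the protocol has already accepted the wait. When the draw is made, blood pressure and cholesterol have been measured on about 20 patients in each of 16 practices, and the rule ignores them.

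With 24 practices per arm, a visible gap in a primary outcome at baseline is quite possible. If arms are then compared only on values at completion, part of that gap carries into the estimate and adds to its variance. With several primary outcomes, an imbalance on one of them also invites argument about that result. The allocation rule cannot be repaired once the draw is made.

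**Working it through.** **Inputs.**
- 48 practices of 20, so 24 practices and 480 patients per arm.
- Blood pressure: "44% of Irish patients with established heart disease have a systolic blood pressure above recommended guidelines (SBP >140 mmHg", with "a design effect size of 1.15 and an intracluster correlation coefficient of 0.011".
- Cholesterol section: 36% above 5 mmol/l, ICC 0.019, design effect 1.27.

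**1. The protocol's own figures.** Design effect = 1 + (m − 1) × ICC with m = 15.
- Blood pressure: 1 + 14 × 0.011 = 1.154 (stated 1.15).
- Cholesterol: 1 + 14 × 0.019 = 1.266 (stated 1.27). Then 500 × 1.27 = 635 and 635 / 0.70 = 907, both as stated.

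The protocol gives no figure for baseline imbalance, so there is none to reproduce.

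**2. Spread of the baseline difference**, with m = 20. SD = √[p(1 − p) × (1 + 19 × ICC) × 2/480].
- Blood pressure: √(0.2464 × 1.209 × 2/480) = 0.0352, or 3.5 points.
- Cholesterol: √(0.2304 × 1.361 × 2/480) = 0.0361, or 3.6 points.

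**3. Chance of a gap of 5 points or more** (normal approximation).
- Blood pressure: z = 5/3.52 = 1.42, P = 15.6%.
- Cholesterol: z = 5/3.61 = 1.38, P = 16.7%.
- At least one, if independent: 1 − 0.844 × 0.833 = 29.6%.

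| Variation | P(at least one ≥ 5 points) |
|---|---|
| Correlation 0.5 between the two differences | 27.4% |
| Stated design effects 1.15 and 1.27 | 27.6% |
| Other baseline rates quoted in the Background | 29.4% to 31.4% |
| No between-practice variance | 21% |
| Simulation, stratified by centre and size (≥ 5 / > 5) | 31.1% / 28.2% |

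A 10-point gap has a probability of about 0.5% per outcome.

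**4. Against the planned effects.** These are 44% × 0.8 − 22% = 13.2 points and 36% × 0.8 − 18% = 10.8 points. Five points is 38% and 46% of them. If 30% to 60% of a gap persists to two years (an assumption; the protocol gives no figure), a 5-point gap shifts the result by 1.5 to 3 points.

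**5. Effect of a constrained draw.** In simulation, choosing at random among the best 10% of 200 candidate allocations per centre, scored on four baseline outcomes, cuts the SDs to 1.5 and 1.6 points. The chance of a 5-point gap in either outcome falls to about 0.1% to 0.3%.

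**6. What that does to the treatment estimate.** Assume a baseline–outcome correlation of 0.5 and ICC 0.019. In standardised units:

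| | Stratified draw | Constrained draw |
|---|---|---|
| Unadjusted completion comparison, SD | 0.076 | 0.067 |
| Baseline-adjusted, SD | 0.0658 | 0.0654 |

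A rough formula agrees. Adjustment multiplies the SD by √(1 − 0.25) = 0.87. The constrained draw alone multiplies it by √(0.75 + 0.25 × (1.5/3.5)²) = 0.89. A second simulation, in percentage points, gave a fall from 3.5 to 2.8–3.0 unadjusted and almost none after adjustment.

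**The case against.** The case on the other side is strong in several respects.

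- **Nothing in the rule is wrong.** An independent person, computer-generated numbers and stratification within centre make a valid randomisation. That stands. Waiting for baseline data is a strength, and centre is balanced too.
- **Chance imbalance is not bias.** That stands. At 70% follow-up there are 336 patients per arm, 14 per practice. The standard error of the effect is then √[(0.352 × 0.648 + 0.22 × 0.78) × 1.143/336] = 3.7 points for blood pressure and √[(0.288 × 0.712 + 0.18 × 0.82) × 1.247/336] = 3.6 points for cholesterol. A shift of 1.5 to 3 points is 0.4 to 0.8 of a standard error.
- **The 30% depends on a chosen threshold and on two outcomes.** That stands, so the per-outcome figures must be given with it. Most of the spread is ordinary patient sampling: with ICC set to zero the SDs are still 3.2 and 3.1 points.
- **Baseline adjustment does nearly the same job.** That stands for precision, as step 6 shows. The article rules out an analysis of change, not baseline as a covariate, and it promises more efficient modelling. The covariate list may properly sit in an analysis plan that is not shown, so its absence is not itself a fault.

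What survives is narrower: the data are in hand, using them costs little, and the comparison as described in the article gains from it.

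**Conclusion.** The point holds as a cheap improvement to consider. The plan accepts a baseline difference with an SD of about 3.5 points in each of two primary outcomes, and a 16% to 17% chance per outcome (about 30% for either) of a gap of 5 points or more, when data to prevent most of this are available at the draw. For an unadjusted completion comparison, the cost is an SD of the effect estimate that could be about 12% lower (1 − 0.067/0.076), or 14% to 20% lower in the second simulation (1 − 3.0/3.5 to 1 − 2.8/3.5). Once baseline is adjusted for, the remaining gain is under 1% (1 − 0.0654/0.0658).

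A reader might infer that the randomisation is biased, that it balances on practice size alone, or that the allocation rule matters whatever the analysis. The documents do not support these readings: the draw is independent and random, each centre is split eight and eight, and the precision gain depends almost wholly on whether baseline enters the model.

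The figures rest on the protocol's rates and ICCs. The 5-point threshold, independence of the two outcomes, 30% to 60% persistence and the correlation of 0.5 are assumptions.

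**What to change.** 1. **Patient identification section.** Keep the timing, the independent person and the size strata. Within centre and size stratum, generate the eight-to-eight allocations and score each on the between-arm difference in practice-level baseline blood pressure control and cholesterol control (admissions optional). Draw one at random from the best-balanced set, for example the best 10%, after checking that no two practices are always together or always apart. SF-12 can be left out: its stated ICC is below 0.0001, so it shows virtually no practice-level clustering.
2. **Randomised controlled trial analysis section.** State that each completion comparison is adjusted for the baseline value of that outcome, and include the balancing variables in the model. This step gives most of the precision.

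**Cost.** A short allocation program and a coded practice-level file for the independent person; no extra patients, visits or measurements. There are two downsides. Baseline entry for the balancing variables must be complete before the draw, which could lengthen the gap to a first intervention consultation meant to follow baseline promptly. Tests are also slightly conservative if the balancing variables are left out of the model. The allocation change is possible only before a centre's draw; the adjustment can be specified later, before outcome data are seen.
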